## Abstract

**Introduction::**

Hypertensive intracerebral hemorrhage (HICH) is the most serious complication of hypertension. Clearing intracranial hematoma as soon as possible, reducing brain cell edema, and controlling intracranial pressure could effectively reduce neuron damage, lower patient mortality, and improve patient prognosis. At present, minimally invasive surgery (MIS) has been widely used and plays an important role in the treatment of HICH. However, it is still in controversies about the choice of surgical treatment and medication treatment for HICH. Therefore, we try to conduct a randomized, controlled, prospective trial to observe the efficacy of MIS treatment against HICH compared with medication treatment.

**Methods::**

Patients will be randomly divided into treatment group and control group in a 1:1 ratio using the random number generator in Microsoft Excel. Stereotactic soft channel minimally invasive intracranial hematoma puncture and drainage treatment and medication treatment will be applied respectively. The outcomes of intracerebral hemorrhage volume, Glasgow coma scale, National Institutes of Health Stroke Scale will be recorded.

**Conclusions::**

The findings of the study will be helpful for the choice of MIS and conservative treatment when treating HICH patients.

**Trial registration::**

OSF Registration number: DOI 10.17605/OSF.IO/ME6Y5.

## Introduction

1

Hypertensive intracerebral hemorrhage (HICH) is the most serious complication of hypertension, which frequently occurs in middle-aged male, especially in winter and spring. It is caused by the weakening blood vessel due to the damage of small arteries in the brain caused by long-term hypertension.^[1,2]^ HICH is a serious cerebrovascular disease which affects about 4 million people worldwide each year with high mortality and disability rate.^[3]^ Clearing intracranial hematoma as soon as possible, reducing brain cell edema, and controlling intracranial pressure could effectively reduce neuron damage, lower patient mortality, and improve patient prognosis.^[4,5]^

The bleeding volume in most patients with HICH is 20 to 40 mL, which is a moderate amount. For those patients, either medication treatment or surgical treatment could be applied. Medication treatment for HICH is the most basic therapeutic choice, including controlling blood pressure and glucose, anti-infection, relieving cerebral edema, fluid infusion, nutritional support, and symptomatic treatment.^[6]^ It shows certain curative effects, but it may also prolong the hematoma compression period to damage brain tissue, which could possibly result in serious neurological deficit. Theoretically, surgery has the potential to rapidly remove the hematoma to reduce brain damage. At present, minimally invasive surgery (MIS) has been widely used and plays an important role in the treatment of HICH. The minimally invasive hematoma evacuation is a simple and quick operation, and it could avoid the injury of brain tissues and blood vessels to reducing the risk of postoperative mortality and complications.^[4,7,8]^

However, it is still in controversies about the choice between surgical treatment and medication treatment for HICH.^[9]^ Although many studies showed that MIS is significantly better than medication treatment,^[10]^ many studies believe that different inclusion criteria could affect the results, and most patients in the surgical treatment group are more severe than those in the medication treatment group, which could also affects the conclusions.^[11]^ In addition, several randomized controlled trials have failed to demonstrate improvement in outcomes of patients in surgical treatment.^[12]^ Therefore, we try to conduct a randomized, controlled, prospective trial to observe the efficacy of MIS treatment against HICH compared with medication treatment.

## Methods

2

### Study design

2.1

This is a single-center, randomized, controlled clinical trial (CHiCTR), approved by the Ethics Committee of traditional Chinese medicine, and it will be carried out in accordance with the Declaration of Helsinki. A flowchart of this study is shown in Figure 1. The study conforms to the Standard Protocol Recommendations for Interventional Trials 2013 Statement,^[13]^ and the results will be reported according to the CONSORT Statement extension for trials.^[14]^

**Figure 1 F1:**
[figure not shown]
Flow diagram of the study.

The protocol will be in accordance with the Helsinki Declaration and approved by the Clinical Research Ethics Committee of our hospital. This experiment has been registered in the open science framework (OSF) (registration number: DOI 10.17605/OSF.IO/ME6Y5). Before randomization, all patients will sign a written informed consent, and they can freely choose whether to continue the trial at any time.

### Participants

2.2

Participants will be mainly recruited from inpatients in Hospital of traditional Chinese medicine. Previous report^[15]^ showed that medication treatment against HICH could reduce intracerebral hemorrhage (ICH) volume in 55% in 7 days. According to our preliminary study, a 7-day-reduction of ICH volume is 82%, and taking *α* = 0.05 and *β* = 0.2, a sample size of 38 will be needed. Considering the loss to follow-up, 46 patients will be ultimately recruited.

Inclusion criteria are:

(1)diagnosed with HICH^[16]^;(2)aged 18 to 75 years old;(3)with 20 to 40 bleeding volume;(4)Glasgow coma scale score of 8 to 12;(5)written informed consent.

Exclusion criteria are:

(1)severe organ dysfunctions or clotting disorders;(2)complicated with ischemic stroke, or nervous system tumors, or mental illness.

### Randomization and blinding

2.3

To minimize selection bias, patients will be randomly divided into treatment group and control group in a 1:1 ratio using the random number generator in Microsoft Excel. The patients and the neurosurgeons will not be blinded, and an independent researcher of no interest with the study will analyze the data.

### Interventions

2.4

Stereotactic soft channel minimally invasive intracranial hematoma puncture and drainage treatment will be performed for patients in the treatment group with the following procedure:

(1)Locate the patient's puncture point, puncture angle, and catheter depth based on the level displayed on the preoperative computed tomography.(2)Mark the puncture point perform local skin anesthesia.(3)Make a 3 cm coronal linear skin incision lateral to the midline over the frontal area, and penetrate the skull with an electric drill. Insert the No. 12 soft channel drainage tube into the hematoma cavity according to the pre-designed direction and depth, pull out the guide core, and then drainage gently with a 5 mL syringe.(4)Perform liquefaction and drainage about 4 hours after the puncture with urokinase.(5)Extubate after the hematoma is basically removed after computed tomography scan.

Conservative treatment will be applied to patients in control group, including controlling blood pressure and glucose, anti-infection, relieving cerebral edema, fluid infusion, nutritional support, and symptomatic treatment.

### Outcome variables

2.5

Vital signs and vital organs functions will be closely monitored. The primary outcomes are ICH volume reduction on day 0, 1, 3, and 7, coma condition measured by Glasgow coma scale and neurological function by National Institutes of Health Stroke Scale at week 0, 1, 2, 4, and then every month for 6 month. Secondary outcomes are activity of daily living at week 0, 1, 2, 4, and then every month for 6 month. Length of hospital stay and complications, and all possible adverse events will be recorded.

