### Statistical methods

2.6

All statistical analyses will be conducted by SPSS version 22 (IBM, Chicago, IL). Measurement data will be described in mean and standard deviation or median and interquartile range, and categorical variables as number and percentage. Different statistic method will be applied according to different data type. *P* < .05 is considered statistically significant.

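### Three repeatedly measured primary outcomes and no single primary comparison: the 5% error rate used to size the trial does not cover the primary claim

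*Protocol article*

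**What the plan says.** Section 2.5 (Outcome variables) names three primary outcomes in one sentence. It opens "The primary outcomes are ICH volume reduction on day 0, 1, 3, and 7, coma condition measured by Glasgow coma scale" and continues with "neurological function by National Institutes of Health Stroke Scale at week 0, 1, 2, 4, and then every month for 6 month". Activity of daily living is the only outcome labelled secondary. None of the three primaries is ranked above the others, no visit is marked as primary, and nothing says whether one, some or all of them must favour surgery.

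Section 2.6 (Statistical methods) says of the analysis: "Different statistic method will be applied according to different data type". For the threshold it says that P "< .05 is considered statistically significant".

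Section 2.2 (Participants) sizes the trial on one quantity at one time. For control, "medication treatment against HICH could reduce intracerebral hemorrhage (ICH) volume in 55% in 7 days"; for surgery, "a 7-day-reduction of ICH volume is 82"%. With alpha set at "0.05 and *β* = 0.2, a sample size of 38 will be needed", rising to 46 after allowance for loss to follow-up.

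**The concern.** The sample size calculation treats the trial as having one decision: day-7 volume reduction, tested at 5%. The outcome section gives it three outcomes of equal standing, each at several visits. The error rate and power in section 2.2 belong to the first design and say nothing about the second.

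Two things are at stake. First, if a significant result on any primary outcome is reported as a positive trial, the chance of a false positive exceeds 5%, and the outcome or visit to emphasise can be chosen after the data are seen. Second, volume and neurological scores may disagree, since drainage removes blood directly but need not improve function. The article gives no rule for what the trial would then conclude, although its stated purpose is to inform the choice between surgery and conservative treatment.

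**Working it through.** **1. The plan's own figure.** Inputs from section 2.2: 55% versus 82% (difference 27 points), alpha 0.05, power 80%, N = 38, taken as 19 per arm under the 1:1 ratio in section 2.3. For means, n per arm = 2·SD²·(z for alpha + z for power)² / difference². No SD is given, so 38 cannot be reproduced. Solving for the SD, two-sided, gives 27 / (2.802 × √(2/19)) = 29.7 points. Read as proportions, the same inputs give 46 per arm (92 in all, two-sided, no continuity correction), which is not 38. On any reading, the calculation concerns one comparison at alpha 0.05.

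**2. Number of primary comparisons (section 2.5).**
- Volume: days 1, 3, 7 = 3.
- GCS and NIHSS: weeks 1, 2, 4 plus monthly visits to month 6 = 8 each if week 4 counts as month 1, otherwise 9 each.
- Total: 3 + 8 + 8 = 19, or 3 + 9 + 9 = 21. If day 0 is a post-procedure scan and is tested, add one.

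These are outcome-by-visit pairs. The distinct post-baseline times number only 10 to 11: days 1, 3, 7; weeks 2, 4; and 5 or 6 monthly visits.

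**3. Chance of at least one P < .05 when there is no effect.** Two-sided tests are assumed; the article does not state sidedness. For k independent tests the chance is 1 − 0.95^k. For correlated tests it comes from simulating normal test statistics (400,000 draws per row).

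One test per outcome (k = 3):

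| Correlation between outcomes (assumed) | Chance |
|---|---|
| 0 | 14.3% |
| 0.5 | 12.4% |
| 0.8 | 9.9% |

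Every visit tested separately:

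| Correlation within / between outcomes (assumed) | 19 tests | 21 tests |
|---|---|---|
| 0 / 0 (upper reference) | 62.3% | 65.9% |
| 0.5 / 0.3 | 47.1% | 49.6% |
| 0.7 / 0.5 | 34.8% | 36.4% |
| 0.9 / 0.5 | 24.9% | 25.5% |
| 0.95 / 0.8 | 16.1% | 16.6% |

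Weaker correlation moves the result towards the upper reference: 0.3 / 0.2 gives 55.3% and 58.5%.

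**4. After a correction.**
- One primary comparison: 5%, with N = 38 unchanged.
- Three comparisons at 0.05/3 = 0.0167: at most 5% (1 − 0.9833³ = 4.9% if independent). With the implied SD of 29.7, an assumption, power for volume at 19 per arm falls from 80% to about 66%. Keeping 80% needs 26 per arm, 52 in all before loss, instead of 38.
- All three required to succeed: no inflation, but the power to win is that of all three jointly, and section 2.2 considers volume only.

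**The case against.** The strongest counter-argument is that the article never says each visit will be tested, nor that any one significant result makes the trial positive. Section 2.5 can be read as a measurement schedule, and one repeated-measures test per outcome fits section 2.6 as well as visit-by-visit testing does. This stands. A reader might infer that any of about 20 results below .05 counts as a positive primary outcome under the plan as written, but the text contains no such rule. With one test per outcome the inflation is two to three times 5%, and with an all-must-succeed rule there would be none. No such rule is stated either.

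It can also be said that a condensed article leaves test models, adjustment and order of testing to an analysis plan that is not shown. That holds for the adjustment method, and its absence is not the point here. The choice of primary outcome, however, is made in this document: three outcomes over all visits, while the sizing uses one outcome at one visit. An analysis plan that named a single primary would have to depart from section 2.5.

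Finally, day-7 volume is not the only defensible primary. The Discussion calls reducing disability and improving quality of life critical, so a sponsor might prefer a functional outcome. That is a scientific choice, but it would need its own sample size.

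**Conclusion.** The point holds. The protocol designates three primary outcomes without a primary time point or a combining rule, and this does not match the single comparison on which the trial is sized. That much follows directly from sections 2.2, 2.5 and 2.6.

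The size of the inflation is less certain. It applies if success on any one primary outcome would be claimed. It is then about 10–14% with one test per outcome and about 16–50% if visits are tested separately, the latter for assumed within-outcome correlations of 0.5 to 0.95. The article gives no correlations. Two stronger readings are not supported. The 62–66% figure requires repeated scores on the same patients to be independent, so it is only an upper reference. And the count of about 20 refers to outcome-by-visit comparisons, not to time points.

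**What to change.** In sections 2.5 and 2.6 and in the registration, name one primary comparison with its visit, significance level and sidedness. Day-7 ICH volume reduction, MIS versus control, at 5% is the one consistent with section 2.2, and it leaves 38 and 46 as they are. Make GCS, NIHSS and the other volume visits secondary. Either test them in an order the sponsor fixes in advance, or report them with confidence intervals and no confirmatory claim.

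If the sponsor prefers to keep three primaries, pre-specify one comparison for each. Test each at 0.05/3, or require all three to succeed, and restate the power, because section 2.2 would no longer support it.

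State whether day 0 and week 0 are baseline values. If they are, do not list them as outcomes.

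Cost: with the single primary, only wording and a registration update, on the same data. The downside is that fewer results can be called significant. Keeping three primaries costs power or patients.

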### Statistical methods

2.6

All statistical analyses will be conducted by SPSS version 22 (IBM, Chicago, IL). Measurement data will be described in mean and standard deviation or median and interquartile range, and categorical variables as number and percentage. Different statistic method will be applied according to different data type. *P* < .05 is considered statistically significant.

## Discussion

3

HICH is a spontaneous cerebrovascular disease caused by the rupture of artery, vein or capillary in the brain.^[17,18]^ The hematoma can cause brain cell edema and increased intracranial pressure, and patients would suffer from neurological dysfunction such as decreased limb muscle strength and impaired consciousness. At present, reducing the disability as much as possible and improve the quality of life of patients are critical in the treatment of HICH. In recent years, the application of MIS to remove intracerebral hematomas is more helpful than conventional craniotomy in improving postoperative recovery, reducing postoperative complications, and raising survival rates. MIS offered promise as a means to maximize hematoma evacuation while minimizing damage to normal tissue. Therefore, we try to carry out a prospective trial to compare the difference of ICH volume reduction, neurological function, and activity of daily living between MIS treatment and medication treatment against HICH. We hope that our results will be helpful for the choice between MIS and conservative treatment when treating HICH patients.
